## Abstract

**Background:**

The number of people with an alcohol use disorder (AUD) was recently estimated to be 63.5 million worldwide. The global burden of disease and injury attributable to alcohol is considerable: about 3 million deaths, namely one in 20, were caused by alcohol in 2015. At the same time, AUD remains seriously undertreated.

In this context, alternative or adjunctive therapies such as brain stimulation could play an important role. The early results of studies using repetitive transcranial magnetic stimulation (rTMS) suggest that stimulations delivered to the dorsolateral prefrontal cortex significantly reduce cravings and improve decision-making processes in various addictive disorders. We therefore hypothesize that rTMS could lead to a decrease in alcohol consumption in patients with AUD.

**Methods/design:**

We report the protocol of a randomized, double-blind, placebo-controlled, parallel-group trial to evaluate the efficacy of rTMS on alcohol reduction in individuals diagnosed with AUD. The study will be conducted in 2 centers in France. Altogether, 144 subjects older than 18 years and diagnosed with AUD will be randomized to receive 5 consecutive twice-daily sessions of either active or sham rTMS (10 Hz over the right DLPFC, 2000 pulses per day). The main outcomes of the study will be changes in alcohol consumption within the 4 weeks after the rTMS sessions. Secondary outcome measures will include changes in alcohol consumption within the 24 weeks, alcohol cravings, clinical and biological improvements, effects on mood and quality of life, and cognitive and safety assessments, and, for smokers, an assessment of the effects of rTMS on tobacco consumption.

**Discussion:**

Several studies have observed a beneficial effect of rTMS on substance use disorders by reducing craving, impulsivity, and risk-taking behavior and suggest that rTMS may be a promising treatment in addiction. However, to date, no studies have included sufficiently large samples and sufficient follow-up to confirm this hypothesis. The results from this large randomized controlled trial will give a better overview of the therapeutic potential of rTMS in AUD.

**Trial registration:**

ClinicalTrials.gov NCT04773691. Registered on 26 February 2021

https://clinicaltrials.gov/ct2/show/NCT04773691?term=[name]&draw=2&rank=5.

## Background

Alcohol use disorder (AUD) is considered a major public health problem in Western societies [1]. In 2015, the number of people suffering from an alcohol use disorder was estimated at 63.5 million, namely 843 per 100,000 people, which represents 8.6% of men and 1.7% of women [2, 3]. The global burden of disease and injury attributable to alcohol is considerable: in 2016, about 3 million deaths (approximately 1/20) worldwide were caused by alcohol [4]. In the EU in 2015, alcohol was responsible for 108 deaths per 100,000 people [2]. Because alcohol is implicated in more than 60 diseases (i.e., vascular, endocrine, and neurological diseases, cancer, etc.), and many non-fatal injuries early in life, the disability-adjusted life years (DALYs) are even higher: in 2016, 5.1% of all DALYs, i.e. 132.6 million DALYs, were caused by alcohol (men: 106.5 million; women: 26.1 million) [2, 4].

At the same time, alcohol use disorders remain seriously undertreated. There is a large treatment gap, given that only around 20% of people in Europe and the USA with a diagnosed AUD actually receive any treatment [5–8]. One of the main reasons is that these patients are not ready to stop drinking and thus are not attracted to the abstinence goals anticipated by the current psychosocial and pharmacological treatments [9]. New treatment strategies that aim to reduce alcohol consumption could make it much easier for patients to ask for help. Thus, new treatments supporting this strategy are required to improve the care of patients suffering from AUD.

In this context, alternative or adjunctive therapies such as repetitive transcranial magnetic stimulation (rTMS) and transcranial direct current stimulation (tDCS), two non-invasive brain stimulation techniques, may play a prominent role. They focally modulate the neuronal excitability of superficial brain regions, and even deeper structures thanks to brain connectivity [10]. Indeed, neuroimaging studies have identified changes in the prefrontal regions of patients diagnosed with addictive disorders, in particular in the dorsolateral prefrontal cortex (DLPFC) [11]. These brain changes were associated with cravings, manifested by an intense desire or urge to consume a drug, and with impaired inhibitory control [10, 12, 13]. Overall, the early results of studies using rTMS and tDCS applied to the DLPFC found a significantly reduced craving levels in various addictive disorders (tobacco, alcohol, marijuana, and methamphetamines) [14–18]. These results were consolidated by a meta-analysis that included 17 studies [11]. In this meta-analysis, random-effects analysis revealed a pooled standardized effect size (Hedge’s g) of 0.476, indicating a medium effect size favoring active stimulation over sham stimulation in the reduction of craving. No significant differences were found between the two brain stimulation techniques, even though their mechanisms of action are somewhat different [11, 19]. Regarding rTMS more specifically, a more recent systematic review, including 26 articles and 748 patients, showed significant reductions in cravings and substance use [20].

Even though these results are encouraging, the vast majority of these studies had small sample sizes and only short-term follow-up. In addition, there was considerable heterogeneity in terms of sample population, study design, and outcome measurements. A majority of these studies focused on clinical symptoms such as cravings instead of assessing more global and pertinent therapeutic effects such as reduced consumption or ability to maintain abstinence, which are the ultimate therapeutic goals for individuals with substance-related and addictive disorders.

We therefore propose to evaluate, for the first time and using a randomized controlled trial (RCT) involving a large sample, the clinical benefits of rTMS in patients with AUD who wish to reduce their alcohol consumption.

## Aims

Our hypothesis is that rTMS, which induces changes in the neuronal activity of the DLFPC that decrease cravings, can lead to a decrease in alcohol consumption in patients suffering from AUD.

Thus, the principal objective of this study is to evaluate, in non-abstinent patients with AUD, the efficacy of 1 week of rTMS (5 consecutive twice-daily sessions) versus placebo in reducing alcohol consumption within the 4 weeks following the treatment. In addition, we will repeat the alcohol consumption measurements periodically during 24 weeks of follow-up.

Moreover, we will assess the effects of rTMS on mood, cognitive behavior, and quality of life. In participants who have AUD combined with tobacco use disorder (TUD), the effect of rTMS on tobacco craving and consumption will be explored.

## Methods/design

### Overview

This is a multicenter, randomized, placebo-controlled, double-blind, parallel-group superiority study comparing 5 consecutive twice-daily sessions of active rTMS versus sham rTMS , with an allocation ratio in the trial of 1:1 (Fig. 1). The study is to be carried out in two French addictology departments (Dijon and Strasbourg), where patients with AUD are treated, and aims to recruit 144 patients with AUD over the course of 2 years. These departments provide consultation to a large number of patients, particularly for alcohol use disorder, among whom the study participants will be recruited. In addition, a communication via the social networks of the main center and through the local press is planned.

**Fig. 1 Fig1:**
[figure not shown]
Study flow diagram

The study protocol was approved by an independent ethics committee (Committee for the Protection of Persons, West V) on 28 June 2020 under the number 2019-A03047-50 and by the French national agency for the safety of medical products and devices (*Agence National de Sécurité des Médicaments et des Produits de Santé*). After providing participants with a complete description of the study, written informed consent will be obtained from each participant.

Each revision will again be submitted to the ANSM and the ethics committee for approval. It will then be the subject of a complete re-editing of the protocol.

The SPIRIT reporting guidelines were applied before submitting this manuscript [21]. The SPIRIT checklist is reported in Fig. 2.

**Fig. 2 Fig2:**

SPIRIT figure

### Inclusion criteria

Patients eligible to be enrolled in this trial: (1) males and females over 18 years of age, (2) meeting the criteria for mild to severe AUD as defined in the Diagnostic and Statistical Manual of Mental Disorders-5th edition (DSM-5) [12], (3) wishing to reduce their alcohol consumption, (4) and having experienced at least one prior attempt to achieve abstinence (unsuccessful or relapse).

### Exclusion criteria

Patients will be excluded if they have, at the inclusion visit, any of the following: (1) breath-alcohol concentration (BAC) > 0 mg per liter of exhaled air; (2) less than 6 heavy drinking days (HDD) in the previous 4 weeks (defined as more than 60 g of pure alcohol in men and 40 g in women consumed in 1 day) [1]; (3) average alcohol consumption below the medium risk level according to World health Organization (WHO) in the previous 4 weeks (≤ 40 g/day for men; ≤ 20 g/day for women) [22]; (4) more than 3 days of abstinence prior to inclusion; (5) a revised Clinical Institute Withdrawal Assessment (CIWA) for Alcohol score ≥ 10 (indicating the need for medication-supported detoxification); (6) concomitant treatment with disulfiram, acamprosate, topiramate, baclofene, naltrexone, or nalmefene; (7) a history of pre-delirium tremens and delirium tremens; (8) DSM-5 substance use disorder other than alcohol or tobacco use disorder; (9) acute psychiatric disorders that have required hospitalization and/or immediate adjustment of psychotropic medications; (10) severe major depression, as defined by 17-item Hamilton Depression scale (HAM-D) ≥ 24 [23]; (11) recent change in psychotropic medication (< 1 month); (12) severe chronic psychiatric disorders including schizophrenia, paranoia, and bipolar disorder types I and II; (13) advanced liver, kidney, cardiac, or pulmonary disease or other acute serious or unstable medical conditions that would compromise a patient’s participation in the study according to the physician’s judgment; (14) contra-indications to rTMS: personal history of convulsive seizures, cerebral vascular accident, pacemaker, neurosurgical clips, carotid or aortic clips, heart valves, hearing aid, ventricular bypass valve, sutures with wires or staples, foreign objects in the eye, shrapnel, other prosthesis, or intracranial ferromagnetic material; (15) women who are pregnant or lactating; (16) women of childbearing potential with a positive urine β–human chorionic gonadotrophin pregnancy test at inclusion; (17) concurrent participation in another trial, employees of the investigator or trial site, and patients protected by law; (18) persons who are not covered by national health insurance; (19) patients, in the opinion of the investigation, not able to complete the TimeLine Follow-Back (TLFB) and to record their daily alcohol consumption in a diary (derived from the TLFB) during the 3 months of the study; and (20) patients who refused to sign the consent form and “safety agreement”.

The “safety agreement” is a paper contract which expressly mentions that if a participant comes to the hospital for a visit or a rTMS session using his/her own car and has a BAC > 0.25 mg/l of exhaled air (which prohibits a person from driving a car in France), he/she will accept to give his/her car keys to the medical staff and authorize the staff to call a member of his/her family or a friend to take the patient home if he/she is unable to use public transport.

### Study process

The study will have three phases (Fig. 1):

1) During the first phase, subjects will be screened using the inclusion and exclusion criteria. Each subject will be given information regarding the implementation of the study and the objectives of the research.

2) The second phase will correspond to both the inclusion of participants and the period of rTMS sessions. This phase will always begin on Monday with 5 steps: (1) participants will be evaluated for study eligibility based on the inclusion and exclusion criteria; (2) after receiving the study information (including information concerning biological samples collected for biomarker assessment) again, they will have to sign the informed consent form (including the completion of the biological samples) and the “safety agreement” after ascertaining that participants have a zero alcohol blood level using breath alcohol concentration, collected by the investigators; (3) a clinical (including TLFB) and biological baseline assessment will be performed (visit 1); (4) included participants will be randomized to active or placebo rTMS; and (5) the first rTMS session will be delivered.

Then, daily sessions will be performed during the following days up to Friday, delivered by a trained operator. Since the treatment lasts only 5 consecutive days, no criteria were defined for discontinuing or modifying allocated intervention. In consideration of these elements, no other specific strategy to improve adherence to the protocol or its monitoring has been planned. The second phase will end by a clinical assessment (visit 2) once the last rTMS session has been delivered.

3) The third phase will be a 6-month follow-up phase without treatment. A clinical assessment will be performed every 4 weeks, and biochemical markers of alcohol consumption will be measured at 1, 3, and 6 months after the end of the stimulation. To promote participant retention and complete follow-up, we will use phone call to reschedule visits if they have been missed, or by default made them by phone.

The management of the patients at the end of the study will depend on the therapeutic results: it will be proposed to follow the reduction strategy in cases of efficacy, or to change the therapeutic goal through abstinence if alcohol consumption has worsened. In addition, no compensation is planned for to those who suffer harm from trial participation.

### Interventions

Patients will receive two consecutive 10 Hz rTMS sessions per day over the right DLPFC on 5 consecutive days. One rTMS session will consist of twenty trains of 50 pulses with an intensity of 110% of the resting motor threshold, separated by 19 intertrains of 30 s (1000 pulses per session). The two daily rTMS sessions will be separated by an interval of 15 min. This scheme of 2 sessions per day with a free interval of 15 min was successfully tested in a study on the treatment of depression [24]. In sum, each patient will receive 2000 pulses per day, and so 10,000 pulses at the end of the week of treatment.

The comparator will be sham rTMS. A placebo-controlled design was chosen as it is easy to apply with rTMS (placebo coil) and because placebo is a gold standard for randomized controlled trial. Moreover, the main aim of this study is not to compare rTMS to reference treatment, but to provide evidence of its efficacy.

We will use a Medtronic MagPro X100 Stimulator (MagVenture) with two types of coils: an MCF-B65 butterfly type coil with external liquid cooling unit (maximum magnetic field on the coil surface of 2.5 teslas) and a MCF-P-B65 sham coil with a magnetic field attenuation of more than 80%. After the randomization, following the arm to which the patient will be assigned (active stimulation or placebo), the operator will install the corresponding coil before the patient enters the room. During the stimulations, the investigators will not have access to stimulation room, only the operators will be able to attend the sessions, to preserve double-blinding.

### Randomization

Randomization will be performed the day of inclusion, online, using the secure CleanWeb^TM^ system by the investigator after identification though a personal password after a final check of the eligibility criteria (website https://chu-dijon.tentelemed.com). Patients will be randomly assigned to one of the two groups in a 1:1 ratio to one of two arms: rTMS active or rTMS placebo. The allocation algorithm, which relies on a minimization approach, is established by the study statistician (Unité de Soutien Méthodologique à la Recherche, USMR, Hospital University of Dijon) before the start of the trial. This allocation is stratified on center and sex. Investigators and patients will be blinded to the treatment assignment. A comprehensive document describing the randomization procedure will be kept in a confidential manner at the USMR.

Emergency unblinding will be performed in an emergency situation when the status of the brain stimulation (real or placebo) must be known to the investigator in order to provide appropriate medical treatment.

### Outcomes

In the “*Guideline on the development of medicinal products for the treatment of alcohol dependence*” for alcohol reduction strategies, the European Medicines Agency (EMA) recommend using a co-primary efficacy outcome, change from baseline in total alcohol consumption (TAC) per month, and reduction in number of HDD [1]. Thus, our principal effective criteria on alcohol reduction will be both the change in TAC from baseline to week 4, defined as mean daily alcohol consumption over 28 days (in g/day), and the number of HDD. Baseline will be defined as alcohol consumption during the 28 days before randomization using the *alcohol Timeline Followback* (TLFB) method, a validated method that retrospectively obtains estimates of daily drinking using a calendar [25, 26]. During follow-up, patients will be asked to report their alcohol consumption on a daily basis.

The secondary evaluation criteria will be the change from baseline to the end of the rTMS sessions, and then for each 4-week period after the treatment up to week 24 in:
TAC (g/day) and number of HDDProportion of subjects with a significant categorical shift in World Health Organization (WHO) risk levels of drinking: low risk (H≤40 g/d; F≤20 g/d), medium risk (H≤60 g/d; F≤40 g/d), high risk (H≤100 g/d; F≤60 g/d, and very high risk (H> 100 g/d; F> 60 g/d) [22]Proportion of subjects with a 50%, 70%, and 90% reduction in alcohol consumption as well as the proportion of patients who potentially achieve abstinenceLevel of alcohol dependence severity (alcohol dependence scale)Craving/urge to drink assessment (visual analogue scale, obsessive compulsive drinking scale)Clinical global impression-severity and improvementScores for depression scales (HAM-D—17 items)Quality of Life (short form health survey—12 items)

Other secondary evaluation criteria will include the change from baseline at week 4, week 12, and week 24 after the treatment, in:
Biochemical alcohol consumption markers (gamma glutamyl transferase, mean corpuscular volume, aspartate aminotransferase, alanine aminotransferase, and carbohydrate deficient transferrin)Cognitive assessment (Montreal cognitive assessment)Number of cigarettes smoked/day and craving for tobacco (visual analogue scale, tobacco craving questionnaire) for smokers.

Number of patients with adverse events will be determined at the time of each visit.

No genetic or molecular analysis is planned.

### Sample size calculation

The sample size was calculated using PASS software (version 11, Kayesville, UT, USA) [27]. As the primary efficacy outcome, the EMA recommend using both TAC and the number of HDD [1]. Besides, any reduction in total alcohol consumption of at least 10 g/day for patients with alcohol use disorders will reduce the annual and lifetime risk of alcohol-related death [28].

In this context, the sample size calculation based on an expected difference between the treatment groups of 15 g/day in total alcohol consumption or 3 days per month, with a standard deviation for the TAC of 30 g/day and with an autocorrelation of 0.3 to 0.7 between observations in the same subject, between 82 and 122 patients, would be required.

Considering a significance level of 1.25% (co-primary outcome) and a power of 80%, and with the hypothesis of a premature withdrawal or a non-initiation of treatment (acute repeated alcoholism) for 20% of individuals, 144 patients (72 per group) should be included to meet the objectives of the study.

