### Statistical analysis

All randomized participants will be analyzed regardless of the treatment allocated (intention to treat analyses (ITT)) and after excluding patients with deviation from the protocol (per-protocol analyses (PP)).

The main analysis will be carried out with the intention to treat population. The co-primary outcome of change from baseline in TAC and reduction in the number of HDD at 4 weeks after treatment and its association with rTMS will be analyzed under the intention-to-treat principle using a mixed model for repeated measures.

The baseline and demographic characteristics of the two groups (active rTMS vs sham rTMS) will be described in terms of numbers and percentages and quantitative variables in means and standard deviations, or medians and interquartile intervals. The comparability of the two groups at baseline will be evaluated using the chi-squared test or Fisher’s test for qualitative variables, and Student’s T test or the Wilcoxon-Mann-Whitney test for continuous variables. Then, a mixed model repeated measures will be conducted to estimate the effect of treatment on TAC first, and HDD second. Observed cases will be considered random effects, and site, sex, time, and treatment as fixed effects. We will use multiple imputation techniques to compensate for potential bias introduced by missing endpoint data [29].

For the primary outcome, per-protocol analysis will also be conducted among participants who have completed baseline and endpoint assessments. The secondary outcome measurements will be analyzed with similar models to those used for the co-primary, continuous variables and logistic regression for dichotomized outcomes.

No interim analysis is planned.

All tests will be one-sided. The primary results will be examined at a significance level of 0.0125 (co-primary outcome). For secondary outcomes, the threshold for significance will be fixed at 0.025. All analyses will be performed using SAS version 9.4 (SAS Institute Inc) by the team of statisticians of the Unité de Soutien Méthodologique, Direction of Clinical Research, University Hospital of Dijon, France. Statistical code will not be made public.

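### The 82 to 122 patient range matches an average over three repeated measurements, whereas the primary endpoint is one 28-day value at week 4, so the stated 80% is not shown to be the power of the primary test

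*Protocol article*

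**What the plan says.** In the Protocol article, Sample size calculation starts from an "expected difference between the treatment groups of 15 g/day in total alcohol consumption or 3 days per month". The assumed variability enters the same sentence as "with a standard deviation for the TAC of 30 g/day". The section concludes that, "with an autocorrelation of 0.3 to 0.7 between observations in the same subject, between 82 and 122 patients, would be required". It gives neither the number of observations per patient nor the correlation that belongs to each end of the range. The error rate and power follow: "Considering a significance level of 1.25% (co-primary outcome) and a power of 80" per cent. After a 20% allowance for withdrawal or non-initiation, the target is set: "for 20% of individuals, 144 patients (72 per group) should be included to meet the objectives of the study".

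Statistical analysis fixes the direction and level of testing: "All tests will be one-sided. The primary results will be examined at a significance level of 0.0125 (co-primary outcome". Overview gives the design "with an allocation ratio in the trial of 1:1".

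Outcomes makes the primary TAC criterion the change from baseline to week 4, "defined as mean daily alcohol consumption over 28 days (in g/day"). Baseline is the corresponding mean over the 28 days before randomisation. The same section lists TAC and heavy drinking days in each later 4-week period, up to week 24, as secondary. Study process schedules follow-up assessments every 4 weeks. Aims and the Trial registration data table also place the primary comparison at 4 weeks.

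Statistical analysis proposes a mixed model for repeated measures for the co-primary outcome at 4 weeks. Its fixed effects are site, sex, time and treatment. Neither a baseline covariate nor a treatment-by-time interaction is listed.

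**The concern.** The reported range depends on a correlation between repeated observations, but the declared endpoint has one follow-up value per patient. Averaging several post-treatment values per patient lowers the variance, so fewer patients are needed. That saving is not available to a test of one 28-day mean.

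The direction of the dependence differs too. When post-treatment values are averaged, the required number rises with their correlation. When a single follow-up value is compared with or adjusted for its baseline, the required number falls as the baseline-to-follow-up correlation rises. A low correlation is favourable in the first calculation and unfavourable in the second.

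This paragraph is the article's only justification for 144 patients. A null result at week 4 would be read against a claimed power of 80% that appears to have been computed for a different comparison.

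**Working it through.** **Inputs.** Difference 15 g/day, SD 30 g/day, correlation (rho) 0.3 to 0.7, power 80%, 20% loss and 144 randomised (Sample size calculation); one-sided 0.0125 (Statistical analysis); 1:1 allocation (Overview). The normal quantiles are 2.2414 and 0.8416. The standardised difference is 15/30 = 0.5.

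**Step 1: one value per patient.** Total N = 4 × (2.2414 + 0.8416)² / 0.5² = 152.1, or 77 per arm and 154 in total after rounding up. This is already above the whole reported range.

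**Step 2: reproducing the plan's range.** For the mean of M equally correlated measurements, N is multiplied by (1 + (M − 1) × rho)/M.

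| M | rho 0.3 | rho 0.7 |
|---|---|---|
| 2 | 98.9 | 129.3 |
| 3 | 152.1 × 0.533 = 81.1 | 152.1 × 0.800 = 121.7 |
| 4 | 72.2 | 117.9 |

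Rounding M = 3 up to whole patients per arm gives 41 and 61, hence 82 and 122, an exact match at both ends. First-order autoregressive correlation with M = 3 gives 76 and 116 after rounding. Other variants were tried: M from 1 to 29; equal and autoregressive correlation; change-score and baseline-adjusted forms; alpha 0.0125, 0.025 and 0.05, one- and two-sided; power 80% and 90%. The only other match was two-sided 0.025 with M = 3, which has the same critical value.

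**Step 3: numbers for the week-4 endpoint.** Two assumptions are added here: SD 30 is the SD of a single 28-day value, and 0.3 to 0.7 is also the baseline-to-week-4 correlation. A change score then multiplies 152.1 by 2(1 − rho), and baseline adjustment multiplies it by 1 − rho².

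| Analysis | rho 0.3 | rho 0.5 | rho 0.7 |
|---|---|---|---|
| Change score, N for 80% | 212.9 | 152.1 | 91.2 |
| Baseline-adjusted, N for 80% | 138.4 | 114.1 | 77.6 |

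Both rows fall as rho rises, the opposite of Step 2.

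**Step 4: power with the planned enrolment.** 144 × 0.8 = 115.2 evaluable, or 57.6 per arm. For one unadjusted value the standard error is 30 × √(2/57.6) = 5.59. Then 15/5.59 − 2.2414 = 0.442, which corresponds to 67% power. The other rows replace 30 by 30 × √(2(1 − rho)), 30 × √(1 − rho²) or 30 × √((1 + 2 × rho)/3).

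| Analysis | rho 0.3 | rho 0.5 | rho 0.7 |
|---|---|---|---|
| One value, unadjusted | 67% | 67% | 67% |
| Change score | 51% | 67% | 89% |
| Baseline-adjusted | 72% | 80% | 94% |
| Mean of three values (the inferred method) | 92% | 85% | 78% |

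Rho means the baseline-to-week-4 correlation in the second and third rows, and the correlation among the averaged values in the last. The check covers TAC only; the article gives no SD for heavy drinking days.

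**The case against.** The best defence is the analysis model. Statistical analysis lists time and treatment but no treatment-by-time term. Read literally, its treatment effect is an average over time, which is the kind of quantity the sample-size method powers. That reading is open, but it does not rescue the figure: on the 4-week schedule it would average in periods that Outcomes makes secondary, against an endpoint placed at week 4. It moves the fault to an inconsistency between endpoint, model and sample size, which still has to be resolved. Patients do record consumption daily, but Outcomes reduces the 28 days to one mean.

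Several limits on the evidence stand. Three measurements is a back-calculation, unique only among the variants tried, and the full protocol may state the number. The correlation in the article is between observations in the same patient, so using it as a baseline-to-week-4 correlation is an assumption. So is treating 30 g/day as the SD of a single value: if it is the SD of the change, the correlation-dependent change-score figures do not apply. The 115 evaluable patients assume that the 20% supply nothing, although all randomised patients are to be analysed with multiple imputation. If all 144 contributed full information, power would be about 78% unadjusted and 82% with baseline adjustment at 0.3. These are upper bounds, because imputation does not restore full information.

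A reader might infer that the trial is underpowered. The documents do not support that: several cells in the table reach or exceed 80%. A reader might also infer that 122 at a correlation of 0.7 was adopted as a worst case. The article does not say so, and 144 is not visibly built on 122, since 122/0.8 = 152.5.

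**Conclusion.** The point holds as a mismatch between the sample-size method and the primary endpoint. The arithmetic itself is sound for the comparison it appears to describe. That comparison, a mean of three equally correlated values, is not the change to one 28-day value at week 4. The stated 80% is therefore not shown to be the power of the primary TAC test.

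The size of the discrepancy depends on inputs the article does not settle. On the assumptions in the working, power ranges from 51% to 94% according to analysis and correlation. The gap is widest at a correlation of 0.3, where the inferred method implies 92% and the week-4 endpoint gives 51% to 72%. At 0.7 the order reverses for the change-score and baseline-adjusted analyses. The 80% for a baseline-adjusted analysis at 0.5 agrees with the stated power only by coincidence, because the listed model has no baseline covariate.

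**What to change.** 1. In Sample size calculation, redo the calculation for week-4 TAC. State the number of measurements per patient, whether 30 g/day is the SD of a single 28-day value or of the change, and the assumed baseline-to-week-4 correlation. Restate the power across that correlation range with 144 randomised and 20% loss.

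2. In Statistical analysis, add baseline TAC and a treatment-by-time term to the mixed model, and name the week-4 treatment contrast as the primary test. The 72%, 80% and 94% figures then apply, under the assumptions given. With baseline as a covariate, the treatment estimate is the same whether the outcome is week-4 TAC or its change, so the declared endpoint can stay.

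3. If the model is not amended, report the unadjusted or change-score figures instead (67%, or 51%, 67% and 89%). Quoting baseline-adjusted power for a model without baseline would again give the power of a different analysis.

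The cost is a rewritten sample-size paragraph, two added model terms and a stated power that is less favourable at low correlation. No added enrolment is proposed.

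### After the stated 20% loss, 144 randomised leaves about 115 patients, which does not cover the upper end (122) of the plan's own sample size range

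*Protocol article*

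**What the plan says.** The Sample size calculation section takes an "expected difference between the treatment groups of 15 g/day in total alcohol consumption or 3 days per month", a "standard deviation for the TAC of 30 g/day" and an "autocorrelation of 0.3 to 0.7 between observations in the same subject", and concludes that "between 82 and 122 patients, would be required". The next paragraph gives the error rate and power: "Considering a significance level of 1.25% (co-primary outcome) and a power of 80" percent. It makes one allowance covering both early withdrawal and failure to start treatment, "for 20% of individuals, 144 patients (72 per group) should be included to meet the objectives of the study".

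The Statistical analysis section adds that "All tests will be one-sided" and that "The main analysis will be carried out with the intention to treat population".

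The article does not say which correlation in the range the 144 is meant to cover, how many repeated measurements were assumed, or how the 20% was applied.

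**The concern.** The base, the loss rate and the final number are all printed, and they do not agree at the upper end of the range. A reader is told without qualification that 144 meets the study's objectives across a planning range that extends to a correlation of 0.7. With 20% removed, the remaining number is below what the plan says it needs there.

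A second problem lies in the allowance itself. A patient with no outcome data reduces the number analysed. A patient who is randomised but never stimulated stays in the intention-to-treat analysis and pulls the observed difference towards zero. Inflating the sample size deals with the first and not the second, yet the plan puts both into one 20%.

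At stake is the accuracy of the power statement on which the trial's size is justified.

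**Working it through.** **Inputs from the protocol article.** Difference 15 g/day; SD 30 g/day; correlation ρ from 0.3 to 0.7; level 0.0125; power 80%; 20% loss; 144 randomised (all from Sample size calculation). One-sided tests (Statistical analysis). 1:1 allocation (Overview).

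**Assumption.** The number of measurements M is not stated. I take M = 3 with equal correlation between all pairs (compound symmetry), because this returns both printed figures. Other values of M from 1 to 7, first-order autoregressive correlation, a change score and a baseline-adjusted analysis did not return both at a one-sided 0.0125.

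**Step 1. Reproduce 82 and 122.**

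n per arm = 2 × (30/15)² × (z₀.₉₈₇₅ + z₀.₈₀)² × (1 + 2ρ)/3

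The z-values are 2.2414 and 0.8416; their sum squared is 9.505, so the leading factor is 8 × 9.505 = 76.04.

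- ρ = 0.3: 76.04 × 1.6/3 = 40.6, so 41 per arm, 82 in total.
- ρ = 0.7: 76.04 × 2.4/3 = 60.8, so 61 per arm, 122 in total.

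Both match exactly.

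**Step 2. Apply the loss.** This needs only the printed 122, 20% and 144.

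- 144 × 0.80 = 115.2, about 7 fewer than 122.
- 122/0.80 = 152.5, so 153, or 154 (77 per group) with equal arms.
- Multiplying by 1.2, which is the wrong operation, gives 122 × 1.2 = 146.4, which is not 144 either.
- Largest loss at which 144 still leaves 122: 1 − 122/144 = 15.3%.
- The lower end is covered: 82/0.80 = 102.5, so 103.

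**Step 3. Power with 115 evaluable, all of the 20% being missing outcomes.**

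Power = Φ(15/(σ × √(4/115)) − 2.2414), with σ = 30 × √((1 + 2ρ)/3)

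| ρ | σ (g/day) | Power |
|---|---|---|
| 0.3 | 21.91 | 92% |
| 0.5 | 24.49 | 85% |
| 0.7 | 26.83 | 77.5% |

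The largest ρ keeping 80% solves 2 × 76.04 × (1 + 2ρ)/3 = 115, so ρ = (3 × 115/152.08 − 1)/2 = 0.63.

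**Step 4. Illustrations with non-initiators kept in the analysis.** The split of the 20% is not given. I assume that non-initiators have outcome data and get no benefit, and take ρ = 0.7.

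- Half of the 20% are non-initiators: 10% missing leaves 129.6 evaluable, of whom 14.4 (11.1%) did not start. The difference becomes 15 × (1 − 0.111) = 13.3 g/day and power Φ(2.828 − 2.2414) = 72%.
- All of the 20% are non-initiators: 144 analysed, difference 15 × 0.80 = 12 g/day, power Φ(2.683 − 2.2414) = 67%.

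At ρ = 0.5 the first case still gives 80%.

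**The case against.** The strongest reply is that the plan gives a range and never names 122, or a correlation of 0.7, as its target. That is right. A reader might infer that 0.7 is the planning value and that the 80% claim fails outright; the article does not support this. The 115 left after loss lies within 82 to 122, and on the reconstructed formula power is above 80% for most of the stated range. What remains is that the article quotes the range up to 0.7 and says, without limiting the correlation, that 144 suffices.

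Second, 115 is a cautious count. The mixed model can use partial data from patients who withdraw, and the Study process section provides for missed visits to be rescheduled or done by telephone. Losses may therefore cost less than a full 20%. This has force, but the 20% is the plan's own figure. The multiple imputation named in the Statistical analysis section does not recover lost information.

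Third, randomisation and the first stimulation session fall on the same visit, after a breath-alcohol check, so non-initiation after randomisation may be rare. The 67% case is an extreme, and a reader should not take it as the expected power. Both dilution cases are illustrations.

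Finally, a two-sided 1.25% test with three measurements at a correlation of 0.7 also gives 144. That does not rescue the figure: it leaves nothing for loss, conflicts with the one-sided tests, and does not yield 82 to 122.

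**Conclusion.** The statement is wrong as written, by a modest amount. The arithmetic gap needs no assumption: after 20% loss, 144 leaves 115, not 122, and covering 122 would take 153 patients (154 with equal arms), 9 or 10 more. The power figures rest on three compound-symmetric measurements, which is inferred from the exact match to 82 and 122. On that basis the 80% claim fails only for correlations above about 0.63, and by about 2.5 points at 0.7.

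The pooling of withdrawal and non-initiation could matter more than the rounding gap, but its size depends on a split that the article does not give. The check concerns total alcohol consumption only, since no SD is printed for heavy drinking days. Nothing here shows that the trial is underpowered across its planning range.

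**What to change.** Keep 144 and restate what it supports, naming the correlation and number of measurements used. Suggested wording, if three measurements is confirmed:

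*With three equally correlated measurements, a 15 g/day difference, SD 30 g/day and a one-sided level of 0.0125: if the whole 20% are missing outcomes, 144 randomised leaves about 115 evaluable, giving 80% power for correlations up to about 0.63 and 77.5% at 0.7.*

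Then split the 20%. Divide by one minus the missing-outcome rate for patients without data, and lower the expected intention-to-treat difference for those who do not start. Give the assumed share of each and the resulting power.

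The cost is a few sentences and a slightly less favourable power figure; recruitment, conduct and analysis do not change. If 80% power at a correlation of 0.7 is wanted with the whole 20% as missing outcomes, the alternative is 154 randomised, 10 more patients; that would still not allow for dilution by non-initiators.
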